## 10.2 Monitoring of patients treated with combination therapy

During administration of sorafenib and vinorelbine, in both study phases, patients will be routinely assessed for adverse events and cell blood count on days 1 and 8 of every cycle.

A complete biochemical blood analysis will be routinely performed at day 1 of each cycle.

Blood samples will be collected on the same day of therapy administration, or, in case of necessity, within the preceding 24 hours.

Physical examination, laboratory testing and evaluation of adverse event will be performed more often, if clinically indicated.

Only for patients treated during the phase I (dose escalation) part of the study, additional blood samples will be collected for cell blood count on day 15 of the first two cycles and for hepatic function markers on day 8 and 15 of the first two cycles. The utility of maintaining these additional tests for patients treated in the phase II cohort will be discussed by the investigators after completion of the phase I.

Radiological imaging will be repeated regularly every 6 weeks (two cycles), unless all measurable disease is assessable by physical exam.

Assessment of tumor response will be performed as long as the patient remains on study, or until disease progression for patients removed from the study for other reasons. Patients who achieve complete or partial response will be re-evaluated at least 4 weeks later to confirm the initial observation of response.

A cardiac re-evaluation through 12-lead EKG plus echocardiogram or MUGA scan will be repeated every 12 weeks (4 cycles), or more often if clinically indicated.

Patients receiving sorafenib monotherapy, after documented disease control, will be assessed for adverse events, cell blood count and biochemical blood analysis on day 1 of 21-day cycles for the first 8 cycles of sorafenib monotherapy, and every 2 cycles (42 days) thereafter, until patient's removal from the study. Physical examination, laboratory testing and evaluation of adverse events will be performed more often, if clinically indicated.

Chest X-ray, bone scan, abdomen ultrasound will be repeated if clinically indicated or, for patients in study more than 12 months, approximately once a year.

All patients will be followed for a minimum of two years for survival.

schematic layout of procedures planned for regular assessment of patients on study.

|                       |            |  |               |                |                |                |                |                |                                 |
|-----------------------|------------|--|---------------|----------------|----------------|----------------|----------------|----------------|---------------------------------|
| Screening             | ≤ 28 days  |  | ≤ 14 days     | X              | X              | X              | X              | X              | Medical/oncological history     |
|                       |            |  |               | X              | X              | X              | X              | X              | Brain CT-MRI scan   |
|                       |            |  |               | X              | X              | X              | X              | X              | 2-D ECHO or MUGA  |
|                       |            |  |               | X              | X              | X              | X              | X              | 12-lead ECG       |
| Combination treatment |            |  |               | X  | X  | X  | X  | X  | Abdomen ultrasound  |
|                       |            |  |               | X  | X  | X  | X  | X  | Bone scan           |
|                       |            |  |               | X  | X  | X  | X  | X  | Chest X-ray       |
|                       |            |  |               | X  | X  | X  | X  | X  | CT-MRI scans of target lesions  |
| Monotherapy           | ≤ 168 days |  | Every 42 days | D. 15          | D. 8           | D. 1           | D. 1           | D. 1           | X                               |
|                       | ≤ 168 days |  | Every 21 days | D. 15          | D. 8           | D. 1           | D. 1           | D. 1           | X                               |
|                       |            |  |               |                |                |                |                |                | X                               |
|                       |            |  |               |                |                |                |                |                | X                               |

|                              |   |   |   |   |  |  |  |
|------------------------------|---|---|---|---|--|--|--|
| Physical examination         | X | X | X | X |  |  |  |
| Signs/symptoms               | X | X | X | X |  |  |  |
| Concomitant medications      | X | X | X | X |  |  |  |
| ECOG PS                      |   | X | X | X |  |  |  |
| Adverse events               |   |   | X | X |  |  |  |
| Drug compliance              |   |   | X | X |  |  |  |
| Hematology       |   |   | X | X |  |  |  |
| Blood chemistry  |   |   | X | X |  |  |  |
| Coagulation     |   |   | X | X |  |  |  |
| Urinalysis      |   |   | X | X |  |  |  |

 To be repeated every 2 cycles (unless all target lesions clinically measurable), before day 1 of the following cycle.

 Only if CT-MRI scan of the thorax not planned.

 To be repeated if clinically indicated, otherwise approximately once a year.

 To be repeated every 4 cycles (~84 days), or more often if clinically indicated

 Only if clinically indicated.

 Comprehensive of: hemoglobin (Hgb), platelet count (Plt), white blood cell count (WBC), white blood cell differential.

 Only for the first 2 cycles in patients treated on the phase I part. If retained necessary, also in patients treated at the RD.

 Comprehensive of: total bilirubin, alanine transaminase (ALT), aspartate transaminase (AST), alkaline phosphatase, total protein, albumin, sodium, potassium, chloride, calcium, blood urea nitrogen (BUN)/urea, creatinine, lipase, amylase, glucose.

 Only: alanine transaminase (ALT), aspartate transaminase (AST)

 Comprehensive of: prothrombin time (PT), international normalized ratio (INR), partial thromboplastin time (PTT)

 Comprehensive of: pH, ketones, protein, glucose, WBC/HPF, RBC/HPF

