## PART I: BACKGROUND AND RATIONALE

### 1. BACKGROUND

Breast cancer is the most common malignancy diagnosed in women. While the incidence of breast cancer is increasing, the mortality has decreased significantly over the last ten years, possibly secondary to earlier diagnosis and the use of adjuvant hormonal/chemotherapy. When breast cancer metastasizes to distant organs, the disease is typically incurable although long-term remissions ( $\geq 10$  years) on hormonal or chemotherapy occur in a small percentage (1-5%) of patients. Chemotherapy, including classical CMF, taxanes, and anthracyclines, produces objective responses in 40-60% of patients. Combination chemotherapy with anthracyclines and/or taxanes produces a higher response rate than CMF with a questionable effect on survival, probably because sequential therapy (ie. adriamycin and/or taxanes) produces responses which negate the effect of using these agents as first line therapy.

On the other hand, second line therapy with docetaxel as compared to mitomycin C/vinblastine results in a higher response rate and overall median survival (11.4 months versus 8.7 months). While these results are significant, it must be emphasized that the difference in median survival is less than 3 months, with a similar quality of life.

Trastuzumab plus adriamycin/cyclophosphamide chemotherapy in patients over-expressing HER2 in their tumors (less than 20% of metastatic breast cancer patients will benefit) shows a clear median survival advantage (over 5 months), but significantly more cardiotoxicity than adriamycin/cytosine chemotherapy alone. The result in this subset of metastatic breast cancer patients represents one of the few reports of a significant median survival advantage over adriamycin/cytosine chemotherapy.

For instance, in a recent randomized trial of FAC vs TAC in metastatic breast cancer, there was no difference in survival or time to progression probable because of sequential use of docetaxel in the FAC group.

Metastatic breast cancer is a virtually incurable disease, for which achieving an objective response to therapies has a questionable effect on survival, and, in many cases, aggressive treatment is not justified. Rather, there is a need to develop and assess new combinations that might maintain a good efficacy profile, without significantly compromising patients' quality of life.

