## 7. INCLUSION CRITERIA

Patients meeting the following criteria will be eligible for enrollment:

1. Women affected by histologically proven metastatic breast cancer.
2. Tumor not susceptible to therapy with trastuzumab, defined as FISH negative for HER-2 amplification or immunohistochemistry 0-1+ for HER-2 expression.
3. Female, age  $\geq 18$ .
4. Documented measurable disease by appropriate radiologic imaging according to RECIST criteria (see Appendix E). Lesions in previously irradiated areas are not considered measurable disease, unless progression has been documented post-radiation.
5. ECOG performance status 0-1 (see Appendix B).
6. Life expectancy  $> 6$  months.
7. Adequate bone marrow function, as indicated by:
  - hemoglobin  $\geq 90$  g/L;
  - neutrophils  $\geq 1.5 \times 10^9/L$ ;
  - platelets  $\geq 100 \times 10^9/L$ .
8. Adequate renal function, as indicated by serum creatinine  $\leq 1.5$  times the upper limit of normal and/or Creatinine Clearance calculated as  $>50\%$  lower normal limit, or estimated as  $\geq 50$  ml/min (Appendix C).
9. Adequate liver function, as indicated by:

- bilirubin  $\leq 1.5$  times upper normal limit;
- AST and ALT  $\leq 2$  times upper normal limit.
- 10. Left ventricular ejection fraction (LVEF)  $\geq 50\%$  as measured by either multigated acquisition (MUGA) scan or echocardiogram (ECHO).
- 11. No therapy for breast cancer in the 4 weeks preceding the therapy start.
- 12. Women of childbearing potential must be using adequate contraception and have a negative pregnancy test at the time of enrollment.
- 13. Patient able to understand and give written informed consent.

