## 13. CONCOMITANT MEDICATIONS

### 13.1 Anticancer treatments

No other chemotherapy, anticancer hormonal therapy, or experimental anticancer medications will be permitted during the treatment period.

Biphosphonates for known bone metastases will be allowed only if started prior to or at the same time trial therapy is initiated, but will not be allowed to be initiated during the study participation.

Patient requiring radiation therapy during the study treatment will remain on study only if the metastases do not represent progression of disease.

In these cases, patients should have study drugs withheld during the course of radiation therapy and until recovery (at least 8 days after radiation).

If there is no evidence of radiation recall reaction, such patients may be retreated with study drugs, provided that there is no sign of progression of disease.

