### 14. DISCONTINUATION OF THERAPY AND WITHDRAWAL FROM STUDY

A patient will stop receiving the study treatment and will be withdrawn from the study when any of the criteria is met:

- Progression of disease based on physical examination or radiological

- Patient's inability to tolerate therapy despite dose reduction. This includes allergic reactions not controlled with slower infusions and routine pre-medications.
  - Patient experiencing an adverse event that would mandate a dose reduction below 200 mg qd for sorafenib, or below 20 mg/m^2 for vinorelbine.
  - Withdrawal of informed consent.
  - Patient evaluated as non-compliant by the investigator.
  - Need of new anticancer treatments. Patient requiring palliative radiation therapy should have study drugs withheld during the course of radiation therapy and until recovery (at least 15 days after radiation). Such patients may be retreated with study drugs, provided that the metastases do not represent progression of disease and there is no evidence of radiation recall reaction.
  - Patient with clinical signs or laboratory test results consistent with pregnancy. The pregnancy will be followed up via the Pregnancy Monitoring Form.
- The investigator can discontinue the patient at any time, at his/her discretion.

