#### **16.4 Analysis of primary endpoints**

Confirmed objective responses and stable diseases will be calculated, to determine objective response rate (ORR) and clinical benefit rate (CBR). The 95% confidence interval for ORR and CBR will be constructed using the exact methods.

ORR is defined as the proportion of subjects with confirmed CR or confirmed PR according to the RECIST criteria, relative to the total subjects who receive at least 1 dose of study medication(s).

CBR is defined as the proportion of subjects with clinical benefit response, relative to the total subjects who receive at least 1 dose of study medication(s).

Patients who do not have on-study radiographic tumor re-evaluation (or clinical re-evaluation, when physical examination is indicated to monitor disease state) will be counted as non-responders/non-benefiters in the assessment of ORR and CBR, unless replaced through enrollment of extra-evaluable patients.

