## Confirmation

In some circumstances it may be difficult to distinguish residual disease from normal tissue. When the evaluation of complete response depends on this determination, it is recommended that the residual lesion be investigated (fine needle aspirate/biopsy) to confirm the complete response status.

Patients with a global deterioration of health status requiring discontinuation of treatment without objective evidence of disease progression at that time should be classified as having "symptomatic deterioration". Every effort should be made to document the objective progression even after discontinuation of treatment.

|                |                        |           |                    |             |                  |
|----------------|------------------------|-----------|--------------------|-------------|------------------|
| Target lesions | CR                     | CR        | Non-Target lesions | New Lesions | Overall response |
| CR             | CR                     | CR        | CR                 | No          | CR               |
| CR             | Incomplete response/SD | No        | PR                 | No          | PR               |
| PR             | Non-PD                 | No        | PR                 | No          | PR               |
| SD             | Non-PD                 | No        | SD                 | No          | SD               |
| PD             | Any                    | Yes or No | PD                 | Yes or No   | PD               |
| Any            | Any                    | Yes       | PD                 | Yes         | PD               |

The best overall response is the best response recorded from the start of the treatment until disease progression/recurrence (taking as reference for PD the smallest measurements recorded since the treatment started). In general, the patient's best response assignment will depend on the achievement of both measurement and confirmation criteria.

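### The response window runs to progression with no stop at new anticancer therapy, so a late response or 24-week stable disease under another treatment would count for the combination

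*Protocol*

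**What the plan says.** Four parts of the protocol together define which tumour findings count.

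- **Assessment window.** Section 10.2 continues response assessment while the patient is on study, or "until disease progression for patients removed from the study for other reasons".
- **Best response.** Appendix E, in the text under Confirmation, states: "The best overall response is the best response recorded from the start of the treatment until disease progression/recurrence". It also measures stable disease from treatment start until progression.
- **What is counted.** Section 16.4 says "ORR is defined as the proportion of subjects with confirmed CR or confirmed PR according to the RECIST criteria", with all patients who took at least one dose as denominator. Section 16.2 defines clinical benefit as confirmed responses plus stable disease of 24 weeks or more. Section 16.4 treats patients with no on-study re-evaluation as failures for both rates, unless they are replaced.
- **Other treatment.** Section 14 lists "Need of new anticancer treatments" as a reason for withdrawal separate from progression. Section 13.1 bars other anticancer drugs only while study treatment lasts.

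On radiation, section 13.1 says: "Patient requiring radiation therapy during the study treatment will remain on study only if the metastases do not represent progression of disease". Sections 13.1 and 14 then let such a patient resume study drugs. The only rule on irradiated lesions is inclusion criterion 4 in section 7, which concerns entry: "Lesions in previously irradiated areas are not considered measurable disease, unless progression has been documented post-radiation".

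**The concern.** None of these rules ends the response window when another anticancer treatment starts. Suppose a patient has stable disease on the week-6 scan, is taken off study for toxicity and starts another drug. If she then has a confirmed partial response, the definitions in 16.2 and 16.4 are met. If her disease merely stays stable under the new drug until week 24, she meets the definition of clinical benefit.

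A narrower version concerns radiation. A non-progressing target lesion irradiated on study stays in the sum of diameters, so shrinkage from the radiation can help produce a partial response.

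The Phase II question in section 5.1 is the clinical benefit of this combination, and section 16.1 sizes the trial on a response rate of 43% against 63%. There is one arm, so no control group carries the same error. Misattributed responses or stable disease can only raise the objective response rate (ORR) and the clinical benefit rate (CBR).

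**Working it through.** **1. Who is exposed.** Scans are due every two cycles, that is every 6 weeks (section 10.2). Eight cycles of 21 days are 168 days, or 24 weeks. A patient removed before her first on-study re-evaluation is already a non-responder and non-benefiter under 16.4, unless replaced. What remains is patients who leave without progression after at least one on-study evaluation and who, when they switch, do not yet have a confirmed response (for ORR) or 24 weeks of stable disease (for CBR). For CBR by imaging this is roughly departure between week 6 and week 24. The protocol foresees departures without progression: section 11.7 takes patients with a grade 3 or higher cardiac event off study, and sections 11.9 and 12 remind investigators that other therapies are usually available.

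**2. The plan's own figures.** Inputs from section 16.1: p0 = 0.43, p1 = 0.63, one-sided alpha 0.10, power 80%, N = 27. By the normal approximation,

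n = [(z0.90·√(p0·q0) + z0.80·√(p1·q1)) / (p1 − p0)]² = 27.08 (stated 27).

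Power at N = 27 for p1 = 53, 58, 63 and 68% is 40.9, 61.6, 79.9 and 92.3% (stated 40, 61, 80 and 92%). These reproduce.

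**3. A reference cut-off.** The protocol gives no number of responders for success. By the exact binomial with N = 27 and p = 0.43, P(X ≥ 15) = 0.131 and P(X ≥ 16) = 0.066. The smallest cut-off with exact one-sided alpha at or below 0.10 is therefore 16.

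**4. Effect per misattributed response.** Each adds 1/27 = 3.7 points to ORR. If k patients who do not respond to the combination are counted as responders, 16 is reached whenever the true count is at least 16 − k:

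| k | P(X ≥ 16 − k), p = 0.43 | Same with a cut-off of 15 |
|---|---|---|
| 0 | 6.6% | 13.1% |
| 1 | 13.1% | 23.0% |
| 2 | 23.0% | 36.2% |

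**5. Expected effect under an assumption.** The protocol gives no switching rate. Assume that a share g = 5–20% of non-responders switch before progression, and that a share q = 20–40% of those respond. Then the observed rate is p = 0.43 + 0.57·g·q.

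- Low end: 0.43 + 0.57 × 0.05 × 0.20 = 0.436; P(X ≥ 16) = 7.4%.
- High end: 0.43 + 0.57 × 0.20 × 0.40 = 0.476; P(X ≥ 16) = 15.3%.

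In patients, 27 × 0.57 × g × q is 0.15 to 1.2 extra responders.

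**6. CBR.** Each misattributed case again adds 3.7 points. No false-positive rate can be given, because section 16.1 states no reference value for CBR.

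**The case against.** The strongest reply is that section 10.2 is a monitoring rule. It says how long tumours are assessed, not which assessments count, and following patients to progression after they leave is right for time to progression (TTP) and progression-free survival (PFS). Section 5.1 speaks of benefit under this combination. A rule for subsequent therapy is also often left to an analysis plan, which is not at hand.

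Part of this stands. The protocol never says outright that responses to later therapy count. A reader might infer that it does, but this follows only from applying 10.2, Appendix E, 16.2 and 16.4 together. Continued scanning is sound. The reply does not remove the point, because Appendix E fixes the best-response window as ending at progression, and 16.4 already settles how some early leavers are classified. The window is set here, and set too wide.

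Three stronger readings are tempting and not supported.

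- **Any early leaver who switches becomes a responder.** A patient who stops in cycle 2 will usually have had no on-study scan. Unless her disease is followed by physical examination, 16.4 already makes her a failure or lets her be replaced.
- **A false-positive rate of 14–40%.** Section 1 says other chemotherapy "produces objective responses in 40-60% of patients". If 10–20% of all patients switched and responded at that rate, ORR would be 0.43 + 0.10 × 0.40 = 47% to 0.43 + 0.20 × 0.60 = 55%, with P(X ≥ 16) of 13.9% to 40.3%. The arithmetic is right, but the document gives no switching rate. The upper end needs 0.20/0.57 = 35% of non-responders to switch without progression, and applies a general range to patients already treated on study.
- **Inclusion criterion 4 contradicts on-study radiation.** It is an entry rule and is silent on follow-up. Appendix E classes bone lesions as non-measurable, so irradiating them does not change the target sum. The gap exists only for a non-progressing measurable target lesion.

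**Conclusion.** The point holds in this limited form. For patients who leave without progression after at least one on-study evaluation and then start another treatment, the response window and endpoint definitions credit later responses, and stable disease reaching 24 weeks, to vinorelbine plus sorafenib. The same holds for radiation shrinkage of a measurable target lesion.

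The direction of the bias is certain, but its size is not, because the number of such patients cannot be known from the protocol. One misattributed response is enough to take the exact error of a 16-of-27 rule from 6.6% to 13.1%, above the nominal 10%. Under the assumed switching and response shares the error is about 7–15%. Both results take a true rate of 43% and the cut-off of 16, which is derived here and not stated in the protocol. The correction should be made because the trial is small, single-arm and read against a historical rate. Sample size and stated power are not affected.

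**What to change.** Add to sections 16.2 and 16.4, with a cross-reference from the best-response text in Appendix E:

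- Only tumour assessments made before the first non-protocol systemic anticancer therapy count toward objective response and toward stable disease of 24 weeks or more.
- A patient who starts such therapy without a confirmed response is a non-responder. One who also lacks 24 weeks of documented stable disease by then is a non-benefiter.
- Shrinkage of a target lesion irradiated on study does not count toward complete or partial response. Radiation alone does not make the patient a non-benefiter, since she may resume study drugs under sections 13.1 and 14.

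Keep the scanning rule in 10.2 so that later scans remain available for TTP and PFS, and record the start date of any new anticancer therapy on the case report form.

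The cost is a short addition to the text and one date field, with no change to treatment, visits or sample size. The downside is that reported ORR and CBR may be slightly lower.

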### 3.2. Toxicity of sorafenib

Sorafenib monotherapy is generally well tolerated, with few side effects. The main toxicities reported at 400 mg twice daily continuously are gastrointestinal (~60%) and dermatologic (~40%) in nature.

Diarrhea, the most common gastrointestinal adverse event (~20%), in most cases is mild to moderate in severity, being reported of grade 3 in 4-8% of patients. Grade 3 diarrhea typically resolves within 24 to 48 hours of drug withdrawal, while GI-2 diarrhea is easily managed with oral loperamide, without drug withdrawal.

Hand-foot syndrome (HFS) is reported in ~60% of patients, being Grade 3 in 6-13% of patients. It manifests with digital desquamation and discomfort or painful symmetrical erythema/edema of palms and soles, often preceded or accompanied by paraesthesias. This toxicity is reversible with temporary drug suspension, and restoration of full doses is possible after its resolution.

Cutaneous rash (typically a facial/scalp erythema) is also frequent (32%-62%), of moderate severity in 6%-10% of cases. Grade 1-2 pruritus is reported in 22% of cases. Alopecia is a rare event.

Fatigue is common (39-56%), but of Grade 3 in only 6% of patients.

Grade 3/4 hypertension seems to occur with higher incidence in renal cancer patients (24% of the cases), while in other cancers is seldom reported as Grade 3.

Other less common toxicities include nausea (G2 in 4%), anorexia (28%, G2 in 4%), stomatitis (G2 in 4%), serum amylase/lipase increase (4% G3, reversible upon withdrawal of the drug within 2 weeks), serum bilirubin increase, lymphopenia and anemia.

Interestingly, in advanced solid tumors treated with sorafenib, patients reporting skin toxicity or diarrhea have a significantly longer time to progression.

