## 12. DEFINITION OF DOSE-LIMITING TOXICITY (DLT)

Dose-limiting toxicity is defined as one or more of the following:

- 1) Febrile neutropenia, defined as a temperature  $\geq 38.5^{\circ}\text{C}$  in the presence of ANC  $< 1.0 \times 10^9/\text{L}$ .
- 2) Grade 4 neutropenia lasting more than 5 days.
- 3) Grade 4 thrombocytopenia ( $< 25 \times 10^9/\text{L}$ ) or anemia ( $< 65 \text{ g/L}$ ).
- 4) Grade 3 thrombocytopenia ( $< 50 \times 10^9/\text{L}$ ), if lasting more than 5 days.
- 5) Grade 3 AST-ALT increase ( $> 5.0 \times \text{ULN}$ ), if lasting more than 5 days.
- 6) Grade 3 rash, if lasting more than 5 days after suspension of sorafenib.
- 7) Grade 3 diarrhea, if lasting more than 24 hours from suspension of sorafenib and adequate treatment with loperamide or diphenoxylate/atropine.
- 8) Other non-hematological toxicity of Grade  $\geq 3$ , except unpremedicated nausea or vomiting, vinorelbine-induced peripheral phlebitis or extravasation ulceration.
- 9) Impossibility to start the second cycle of therapy within 14 days from the planned day, as a consequence of toxicity.

Any patient experiencing a DLT at any cycle will be evaluated by the investigator, who will assess the utility for the patient of continuing the study treatment at lower doses, rather than definitively terminating his participation to this trial.

No patient experiencing a DLT will be retreated at the same dose. The investigator will evaluate risks and benefits for the patient, being aware of the multiple therapeutic possibilities that are usually available for patients at this stage of disease.

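### Phase I schedules total bilirubin only on day 1 of each cycle, so a brief, silent Grade 3 rise in cycle 1, dose-limiting under Section 12 item 8, could go uncounted

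*Protocol*

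**What the plan says.** Protocol Section 10.2 sets the routine chemistry during combination therapy: "A complete biochemical blood analysis will be routinely performed at day 1 of each cycle". Footnote 8 to the schedule table lists that panel, beginning "Comprehensive of: total bilirubin, alanine transaminase (ALT), aspartate transaminase (AST), alkaline phosphatase" and going on to include lipase and amylase.

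For Phase I patients only, Section 10.2 adds blood samples "for hepatic function markers on day 8 and 15 of the first two cycles". Footnote 9 defines a reduced panel: "Only: alanine transaminase (ALT), aspartate transaminase (AST".

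Blood is already taken at these visits. All patients have counts on days 1 and 8 ("patients will be routinely assessed for adverse events and cell blood count on days 1 and 8 of every cycle"), and in Phase I "additional blood samples will be collected for cell blood count on day 15 of the first two cycles".

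Section 12 names one liver item among the DLTs, item 5: a Grade 3 AST-ALT increase lasting more than 5 days. Item 8 is a residual clause, opening "Other non-hematological toxicity of Grade" and covering Grade 3 and above. It states no minimum duration, and its exceptions do not mention bilirubin, lipase or amylase. Section 9.1 bases escalation on DLTs at the end of the first cycle.

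**The concern.** The Phase I dose decision rests on a count of DLTs in very small cohorts. For that count to be sound, an event that qualifies as a DLT should be looked for during the period in which it counts. ALT and AST are checked weekly in cycle 1, although they count only if Grade 3 lasts more than 5 days. Bilirubin counts at once but has no scheduled mid-cycle check.

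The protocol itself gives reasons to watch it. Bilirubin is a liver-function entry criterion (Section 7, item 9). Section 3.2 includes it among sorafenib's less common toxicities: "serum bilirubin increase, lymphopenia and anemia". Section 4 says the combination is untested in humans and that an interaction through shared CYP3A metabolism must be ruled out.

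An uncounted event can only lower the DLT count, so any error runs toward escalation.

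**Working it through.** There is no sample-size or power figure to reproduce here. The check sets the schedule against the DLT list.

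**Step 1: what is scheduled in Phase I cycle 1.** Inputs are Section 10.2 and footnotes 8 and 9, with footnote 9 read as applying to days 8 and 15.

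| Day | Blood count | ALT/AST | Total bilirubin, lipase, amylase |
|---|---|---|---|
| Cycle 1 day 1 (taken as baseline) | yes | yes | yes |
| Cycle 1 day 8 | yes | yes | no |
| Cycle 1 day 15 | yes | yes | no |
| Cycle 2 day 1 (day 22) | yes | yes | yes |

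The interval between scheduled bilirubin tests is 22 − 1 = 21 days; between scheduled draws it is 7 days. After baseline and up to day 22 there are three draws, one of which includes bilirubin. Section 10.2 allows samples up to 24 hours before treatment, so the day 22 sample may be taken on day 21.

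**Step 2: is a Grade 3 bilirubin rise a DLT?** Items 1 to 4 of Section 12 are haematological. Item 5 covers AST-ALT, item 6 rash, item 7 diarrhoea and item 9 delay of cycle 2. None covers bilirubin, so it falls to item 8. It is outside that item's exceptions (unpremedicated nausea or vomiting, peripheral phlebitis, extravasation ulceration) and needs no duration. The same reasoning applies to lipase and amylase.

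**Step 3: when the count is used.** Under Section 9.1, no DLT among three patients leads to the next level, whereas a DLT leads to up to three more patients at the same level. One uncounted event among three can therefore change the action. Item 9 depends on whether cycle 2 can start, so the cycle 2 day 1 panel falls at the decision point and may inform it. A rise still present then would be seen; one that had resolved would not, unless tested for earlier.

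**Step 4: conditional illustration.** Assume that a Grade 3 episode occurs, that it lasts D days, that its onset is uniform over the 21 days, and that no unscheduled test is done. The chance that a scheduled test meets it is min(1, D/21) now and min(1, D/7) if days 8 and 15 are added.

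| Assumed D (days) | Now | With days 8 and 15 |
|---|---|---|
| 3 | 3/21 = 14% | 3/7 = 43% |
| 5 | 5/21 = 24% | 5/7 = 71% |
| 7 | 7/21 = 33% | 100% |
| 14 | 14/21 = 67% | 100% |
| 21 | 100% | 100% |

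The protocol gives neither the onset nor the duration of such a rise, nor the probability that one occurs. The table shows how the answer depends on D; it does not estimate a miss rate for this trial.

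**The case against.** **The footnote's place is inferred.** No legible table cell carries footnote 9, so linking it to days 8 and 15 rests on content. That stands as a caveat. But day 1 has the complete panel, and Section 10.2 places extra liver tests only on days 8 and 15, so no other placement fits.

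**There is no contradiction in wording.** A reader might infer that footnote 9 conflicts with Section 10.2. It does not: ALT and AST are liver markers, and they match the only named liver DLT, item 5. The mismatch is between this reduced panel and the residual item 8.

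**Bilirubin is not special.** Lipase and amylase share the gap, and Section 3.2 gives them a Grade 3 rate (4%) while giving no grade or frequency for bilirubin. This is right, and it widens the point.

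**Other routes to detection exist.** Section 10.2 permits extra laboratory tests on clinical grounds and assesses adverse events on days 1 and 8. Weekly ALT/AST may itself prompt fuller testing. A rise under continuous sorafenib dosing could also last until cycle 2 day 1. These narrow the concern to a transient, clinically silent rise. They do not remove it, because discretionary testing is not uniform ascertainment.

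**Day 8 vinorelbine.** A reader might infer that day 8 vinorelbine should await a bilirubin result. The protocol sets no such check: Section 11.1 requires only neutrophil and platelet thresholds.

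**Conclusion.** The point holds as a gap in DLT ascertainment. On the routine schedule, the first post-dose bilirubin is cycle 2 day 1, although item 8 would count a Grade 3 rise at any time in cycle 1. The gap affects the Phase I DLT count, can bias it only downward, and leaves the Phase II sample size of 27 untouched.

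Its firm size is one scheduled post-dose bilirubin in 21 days, where blood is drawn three times. A reader might go further and infer that a too-toxic level would probably be cleared, or read the percentages above as the trial's miss rate. The documents support neither, because they give no rate, onset or duration for Grade 3 bilirubin rises.

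The conclusion assumes that footnote 9 belongs to the day 8 and 15 samples and that cycle 1 day 1 serves as baseline. If footnote 9 belongs elsewhere, the analytes for days 8 and 15 are undefined and the same clarification is needed. This is a cheap improvement to a design choice.

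**What to change.** Reconcile footnote 9, Section 10.2 and item 8 of Section 12 so that laboratory toxicities counted as DLTs are measured within the DLT window. State which visits footnote 9 governs. One way is to run total bilirubin, and to consider lipase and amylase, on the Phase I day 8 and 15 samples of cycles 1 and 2; all three assays are already in the footnote 8 panel.

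Cost: 2 days × 2 cycles = 4 extra assays per patient for each analyte. For the 6-12 Phase I patients of Section 6 that is 24 to 48 bilirubin assays, or 72 to 144 for all three analytes, with no extra visit or blood draw. The downside is that slightly more DLTs may be counted. Clinical action on any result stays as in Sections 11 and 12; no dosing or retreatment rule is proposed.
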